### Study procedure

Each cluster will be a PCN, as identified by the NDA. We plan to randomise all 1283 PCNs to one of two interventions or a waitlist control.

Totals of 1150 PCNs and 41,365 patients and an assumed intra-cluster correlation (ICC) of 0.01 and coefficient of variation of 1.62 would provide greater than 99% power to detect a 2 mmol/mol difference in HbA1c between the intervention and waitlist control arm assuming a standard deviation of 18.7 and 10% losses to follow up [17]. This uses the Bonferroni correction to adjust for multiple comparisons (testing two interventions separately against the same control group) with a family-wise type I error rate of 5% (i.e. a 2.5% critical threshold for each comparison).

Estimates for the clustering effects, cluster size and standard deviation are based on the most recent NDA data available from 2021–22. Whilst such reductions in HbA1c are modest at the individual level, they can translate into significant population-level benefits and are comparable to effects by other clinical interventions [18, 19].

### Recruitment

NHS England has 42 ICBs, within which PCNs are nested. NHS England, which commissions the NDA, has a list of ICBs, ICB Clinical Leads and corresponding PCNs. These Clinical Leads include leads for diabetes care, medicines optimisation and practice nurse development. In turn, these ICB Clinical Leads have contact details for the PCNs within their ICB.

Based upon random allocation at the PCN level, ICB leads will be asked to email all PCNs with different messages depending on random allocation to the three groups.

In this way, all PCNs will receive an invite to be involved in work to improve the quality of care. They will not all receive this support at the same time. This is usual practice for the NDA.

We will add to the usual email by informing recipients that the facilitation is being evaluated. Recipients have the option not to engage with the facilitation. Additionally, medium-intensity arm PCNs will be told that this will include observation of what is delivered in the virtual meetings (but not what attendees do). Medium-intensity facilitation arm recipients have the option to attend unrecorded virtual meetings.

### Data collection

Trial outcomes will be assessed using routinely collected individual patient data which is extracted from GP clinical systems by the NDA via the General Practice Extraction Service. We will use NDA-held demographic data in assessing effects on equity. The NDA validates, monitors and reports on data quality [4]; the NDA data quality report provides support that our selected measures are reliable.

The analysis will include outcome data from 12 months before randomisation to 16 months after randomisation.

### Data monitoring

The quality of patient outcome and demographic data is reported and validated by the NDA. A Project Steering Committee (PSC) will meet at least annually to discuss study progress, adherence to protocol, patient safety, and consider new information. A subcommittee of the PSC will be convened where necessary to monitor safety data.

### Data analysis

We will use all available data from all randomised PCNs, according to a detailed pre-specified plan finalised and agreed by the research team before any analyses are undertaken. We will conduct all analyses on the intent-to-treat (ITT) population, in which all PCNs and patients will be included in the analysis according to the group to which they are randomised, regardless of intervention adherence.

We plan no interim analyses except for assessment of progression criteria. We will conduct a single final analysis after the end of the follow-up period, when fully cleaned data are available from the NDA. We will compare characteristics of patients and PCNs lost to follow-up with those not lost to follow-up to assess for attrition bias. A cluster CONSORT diagram will depict the flow of PCNs and patients through the study.

The primary ITT analysis will compare the primary outcome between trial arms, using mixed effects linear regression, with patients nested within PCNs, and with PCNs treated as a random intercept, adjusting for patient-level and PCN-level covariates (including patient age, sex, ethnicity deprivation and PCN-level stratification factors). Estimated mean differences will be reported with confidence intervals, *p*-values and intra-cluster correlation coefficients. For binary outcomes, mixed effects logistic regression will be used and estimated odds ratios will be reported with confidence intervals, *p*-values and intra-cluster correlation coefficients.

Although we expect the level of missing data to be small, we will investigate patterns of missing data and reasons for missing data. We will compare the proportion of missing data between intervention and waitlist control groups. We will build a multiple imputation model assuming data is missing at random for the primary outcome.

Planned subgroup analyses will explore potential moderators of primary outcome treatment effect using key baseline factors (ethnicity, sex, age, and deprivation). This will indicate whether the feedback facilitation contributes towards reducing inequalities in care. Subgroup analyses are exploratory, providing estimates of the direction and size of any interactions.

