### Patient eligibility

All young adults (18–39 years) living with type 2 diabetes and an HbA1c level above or equal to 58 mmol/mol in England in the previous year, identified through the national audit before the intervention period (baseline).

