### Minimisation factors

We will stratify by PCN-level baseline proportion of young adults with type 2 diabetes who have an HbA1c ≥ 58 mmol/mol (above or below median) and by NHS Integrated Care Board (ICB; NHS organisations responsible for planning and commissioning health services for their local populations). ICBs vary by the number of PCNs (median 27; IQR 19 to 42) and number of young adults with type 2 diabetes and raised HbA1c above 58 mmol/mol (median 1732; IQR 1250 to 2498). Stratifying by ICB will help to minimise any imbalances in patient characteristics including age, sex, ethnicity and deprivation, but we will also account for these patient-level characteristics in the statistical and economic analyses.

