### Outcomes

HbA1c level drawn from routine NDA data at 16-months post-randomisation in young adults with type 2 diabetes and baseline HbA1c ≥ 58 mmol/mol. We have chosen a 16-month follow-up period as it allows for a latent period for (i) PCNs and their member general practices to engage with facilitation, plan and initiate changes in clinical practice and (ii) for patients to consult, consider and start any new treatments or make any suggested lifestyle changes and for any benefits to be reflected in subsequent HbA1c measurements.

Secondary outcomes will comprise:Proportion with an HbA1c of < 58 mmol/mol.Proportion with an HbA1c of < 48 mmol/mol.Proportion prescribed both metformin and SGLT2 inhibitor.Proportion in whom the last blood pressure reading (measured in the preceding 12 months) is 140/80 mmHg or less (or equivalent home blood pressure reading).Proportion with statins prescribed.Proportion receiving NICE-recommended care processes in the preceding 12 months: blood pressure check; serum creatinine testing; urinary albumin: creatinine ratio testing; foot examination and risk classification; smoking status; retinal screening; body mass index; and referral to a structured education programme.

In young adults with baseline HbA1c ≥ 48 and < 58 measurement, we will examine the proportion with HbA1c ≥ 58 mmol/mol at follow-up to check for any unintended distributional consequences from focusing resources on those patients with higher HbA1c at baseline.

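### The patient's own baseline HbA1c is not among the covariates named for the primary mixed model, although every eligible patient has one

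*Protocol article*

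**What the plan says.** Under Outcomes, the primary endpoint is "HbA1c level drawn from routine NDA data at 16-months post-randomisation in young adults with type 2 diabetes and baseline HbA1c ≥ 58 mmol/mol". Under Patient eligibility, patients enter because they have "an HbA1c level above or equal to 58 mmol/mol in England in the previous year, identified through the national audit". A pre-intervention HbA1c therefore exists for every eligible patient.

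Under Data analysis, the primary comparison uses mixed effects linear regression with a random intercept for PCN, "adjusting for patient-level and PCN-level covariates (including patient age, sex, ethnicity deprivation and PCN-level stratification factors". The parenthesis is introduced as examples, so the list is not closed. The same section defers detail to a plan that is not shown, "according to a detailed pre-specified plan finalised and agreed by the research team before any analyses are undertaken".

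Three other statements bear on the point:
- Minimisation factors: the only HbA1c-related stratification factor is the "PCN-level baseline proportion of young adults with type 2 diabetes who have an HbA1c ≥ 58 mmol/mol (above or below median".
- Minimisation factors: having named age, sex, ethnicity and deprivation as characteristics that stratifying by ICB should help balance, the section adds "but we will also account for these patient-level characteristics in the statistical and economic analyses".
- Data collection: "The analysis will include outcome data from 12 months before randomisation to 16 months after randomisation". The role of the pre-randomisation values in the model is not stated.

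**The concern.** The baseline measurement of a continuous outcome is usually its strongest single predictor. The article names four demographic covariates and the stratification factors, but not this one.

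The stratification factor cannot stand in for it. It describes the PCN, it is cut at the median, and it counts patients at or above 58 mmol/mol. Everyone in the primary analysis is already at or above 58, so it says little about how far above that threshold a given patient lies.

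Three things are at stake if the model is fitted with the named covariates only:
- Intervals for both intervention-versus-control comparisons, and for the exploratory equity subgroups, are wider than they need be.
- A chance difference between arms in baseline HbA1c passes partly into the estimate.
- The missing-at-random assumption is less credible if it conditions on demographics alone, because whether a follow-up HbA1c is recorded in routine care may depend on how high the baseline was.

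**Working it through.** **Inputs (Study procedure; Randomisation).** 1150 PCNs, 41,365 patients, ICC 0.01, coefficient of variation of cluster size 1.62, SD 18.7, 10% loss, target difference 2 mmol/mol, 2.5% threshold per comparison (taken as two-sided), allocation 1:1:1.

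**Step 1: reproduce the stated power, with no baseline adjustment.** The article does not print its design-effect formula; the usual one for unequal clusters is used.
- Mean cluster size after loss: m = 41,365 / 1150 × 0.9 = 32.37.
- Patients per arm: 41,365 × 0.9 / 3 = 12,410.
- Design effect: 1 + ((1.62² + 1) × 32.37 − 1) × 0.01 = 2.163.
- SE = 18.7 × √(2 × 2.163 / 12,410) = 0.349 mmol/mol.
- Power at 2 mmol/mol: Φ(2/0.349 − 2.241) = 99.98%.

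Reading 41,365 as already net of loss gives 99.99%; losing 10% of clusters gives 99.96%. The stated figure of more than 99% is reproduced, and it owes nothing to baseline HbA1c.

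**Step 2: split the variance.** The design effect has a within-PCN part, 1 − 0.01 = 0.99, and a between-PCN part, 0.01 × (1.62² + 1) × 32.37 = 1.173. More than half of the variance of the comparison is therefore between PCNs. The gain from a patient-level covariate depends on whether it also explains that part.

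**Step 3: add baseline HbA1c, assumed correlation r with follow-up.** The article gives no r; 0.3 to 0.6 is an assumption.
- Within-PCN variance only: SE = 0.349 × √{(0.99(1 − r²) + 1.173) / 2.163}.
- Both levels equally: SE = 0.349 × √(1 − r²).

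| r | SE, within only | SE, both levels | 97.5% CI half-width, within / both | Power at 1 mmol/mol, within / both |
|---|---|---|---|---|
| none | 0.349 | 0.349 | 0.78 | 73% |
| 0.3 | 0.342 | 0.333 | 0.77 / 0.75 | 75% / 78% |
| 0.4 | 0.336 | 0.320 | 0.75 / 0.72 | 77% / 81% |
| 0.5 | 0.329 | 0.302 | 0.74 / 0.68 | 79% / 86% |
| 0.6 | 0.319 | 0.279 | 0.72 / 0.63 | 81% / 91% |

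Over r = 0.3 to 0.6 the SE falls by 2–9% (within only) or 5–20% (both levels). Power at 2 mmol/mol stays above 99.9% throughout; the 1 mmol/mol column is only illustrative.

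**Step 4: chance imbalance.** Assume the baseline SD and ICC equal those of the outcome, so that a one-SE baseline difference is 0.349 mmol/mol. The shift in an estimate not adjusted for baseline is r times the imbalance:
- one SE: 0.3 × 0.349 = 0.10 to 0.6 × 0.349 = 0.21 mmol/mol;
- two SE: 0.21 to 0.42 mmol/mol, against a target of 2.

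**The case against.** The strongest reply is that nothing has been excluded. The covariate list is open, the article condenses a fuller protocol, detail is deferred to a plan that is not shown, and pre-randomisation outcome data are expressly part of the analysis. That plan may already contain the covariate. This stands as far as it goes: a reader might infer that the trial has decided against baseline adjustment and so gives up precision, and the document does not support that. What remains is that the article chose to name covariates and left out the one most closely tied to the outcome. A model without it would be fully consistent with the published text, and one that adds it later could look like a post hoc choice.

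The sentence under Minimisation factors is also weaker evidence than it looks. It refers back to characteristics that stratifying by ICB should help balance; it is not a second specification of the primary model.

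The size is open to challenge too. The 5–20% range assumes that between-PCN variance falls in the same proportion as within-PCN variance. Selection at 58 mmol/mol or above may also pull the correlation towards the low end. Both objections are fair, which is why the 2–9% range is given first. With more than 1,100 PCNs, large chance imbalance is unlikely.

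On missing data, the article lists no variables for its multiple imputation model, so it cannot be said that baseline HbA1c is absent from it.

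Finally, it is tempting to ask for the same adjustment in every binary secondary outcome. In a mixed logistic model an added covariate changes the conditional odds ratio being estimated. That is a choice of estimand with its own consequences, and it does not follow from this point.

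**Conclusion.** The point holds as a gap in a named but open list, not as a fixed exclusion and not as a flaw in the design. The patient's own baseline HbA1c is available by definition, is not named, and is not replaced by the PCN-level split. The planned model without it would be valid, and no stated design figure fails.

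The benefit is narrower intervals and protection against chance imbalance: an SE 2–9% smaller if only within-PCN variance falls, and 5–20% smaller if variance falls at both levels. This rests on an assumed correlation of 0.3 to 0.6 and on the protocol's own ICC, SD and cluster-size variation. It matters most if the true effect is below 2 mmol/mol, and for the equity subgroups. A reader might infer from the omission that the trial is underpowered; the reproduced power rules that out.

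**What to change.** Name the patient's baseline HbA1c, as a continuous variable, among the fixed covariates of the primary linear mixed model, and include it in the imputation model for the primary outcome. Define it as the last value before randomisation, and state how it relates to the previous-year value that makes the patient eligible. If the unseen analysis plan already says this, nothing further is needed beyond consistency with the article.

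The cost is about one line of text. The values lie within the 12-month pre-randomisation window already planned, so no new data are needed. Study progress puts allocation in April 2025, so 16-month follow-up runs to about August 2026. When the article appeared in January 2026, the change could still be made before outcome data were complete.

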### Process evaluation

Our theory-informed, integrated process evaluation will involve semi-structured interviews, documentary analysis, survey data collection and observations, with component study level analysis and synthesis.

Guided by the Medical Research Council Framework for developing and evaluating complex interventions [20], we will:Describe how the targeted teams and individuals engage with each intervention to support improvement activity and how context influences this work.Assess fidelity of design, delivery, receipt and enactment of the interventions.Describe how teams enact tailoring.

#### Theoretical approach

We address criticisms that feedback facilitation interventions are ill-defined [11] by illustrating intervention content in a logic model (Appendix B). The process evaluation will draw upon the intervention programme theory. The interventions were developed through co-design with stakeholders and drawing upon evidence and theory [9, 13, 14]. The interventions have defined content including specified behaviour change techniques [16]. The logic model describes the mechanisms through which these active ingredients stimulate collective actions tailored to the local context to generate important outcomes. As such, the design incorporates mechanisms targeting different levels: individual (behavioural), collective (team working) and organisational. The process evaluation will explore whether hypothesised mechanisms for achieving change throughout professional behaviour (what participants do), care delivery (processes of care) and patient-level outcomes (blood glucose) are evident when the interventions are used in practice, and what wider factors affect these mechanism-outcome relationships.

We will use Normalisation Process Theory (NPT) to conceptualise the dynamic processes (coherence, cognitive participation, collective action and reflexive monitoring) during implementation [14]. We will investigate fidelity [21, 22] to assess the extent to which intervention active ingredients are delivered by facilitation deliverers and received and enacted as intended by participants. We will explore contamination between study arms. We will explore whether and how teams tailor their response to local contexts. This will go beyond the fidelity question of whether participants use the tailoring frameworks within the interventions by exploring how teams select strategies, who is involved in this work and when plans are reassessed.

Our analysis will be ongoing and iterative and draw upon other approaches from implementation science where relevant.

#### Participants

We will include healthcare professionals within PCNs (e.g. clinical pharmacists, GPs, practice nurses, managers) and people involved in intervention delivery (e.g. NDA improvement lead, NDA administrator).

#### Sampling and recruitment

For up to 60 process evaluation PCNs: It is not possible for PCNs to give permission for the study as they are not legal entities. Instead, we will seek permission for the study from sampled practices with a local information pack. We will use strategic sampling within the intervention arms (e.g. by baseline performance) aiming to ensure diversity of teams, settings and population characteristics. Sampling considerations relating to specific data collection activities are described below. We will sample from teams who have and have not registered for the intervention. To limit participant burden, we will sample around 20 teams from each arm. We will give all potential participants information about the study and ask interviewees for written informed consent.

All registering PCNs: Given the scale of study participation and relatively small proportion of PCNs that can be included in the in-depth qualitative work, a brief arm-specific online survey will be sent to all PCNs that have registered for one of the interventions.

Documents (e.g. intervention materials) will be analysed as part of the fidelity assessment. The intervention provider will be asked to share data describing attendance and engagement.

Observations will only happen in the medium-intensity arm where, with informed consent, the virtual workshop deliverers will be observed asynchronously to assess fidelity of delivery using recordings routinely made by the NDA. Recipients will be given a choice to attend virtual workshops which are not observed. We will seek to observe up to 50%; participants will be given information about the study and given the choice to attend virtual workshops which are not observed.

#### Data collection

We will use theory-informed, semi-structured interviews. The data will be used for all three process evaluation objectives and to collect health economics data. In the medium intensity arm: up to 20 interviews after the initial virtual workshop, 10 for implementation, engagement and fidelity and 10 for tailoring, and the same post-intervention; in the low-intensity arm, up to 20, post-intervention; in the waitlist control arm, up to 20 interviews to explore ‘implementation as usual’ and contamination (e.g. receipt and use of any materials shared with intervention arm participants). We will interview approximately 3 intervention deliverers to explore fidelity and gather health economics data. We will analyse approximately 28 h of observations.

The observations will be asynchronous using routine recordings made by the NDA and involve a structured analysis of about 50% of the virtual workshops (28 h) from the medium-intensity facilitation. Observation of delivery will inform assessment of fidelity; Data will also be collected to understand tailoring and cost, to supplement and stimulate interview questions. We will not observe low-intensity or waitlist control arms given higher risk of unintended co-intervention effects.

Both the medium- and low-intensity facilitation ask participants to identify influences upon performance and select strategy(s) to address these influences. We will seek and analyse documents such as action plans to explore fidelity and tailoring. We will seek related documents from waitlist control arm participants to understand ‘implementation as usual’.

To supplement interview data, we will seek permission from the Health Research Authority (HRA) for a survey distributed via Diabetes UK to people who registered for one of the interventions. The brief survey aims to gather structured data about tailoring, fidelity, contamination and cost (described in time, grade and any equipment costs). Data will be used for both the process and economic evaluation, to facilitate comparisons between arms and to help reflect the large number of sites not included in the interviews.

#### Data management and analysis

With written, informed consent, we will audio-record and transcribe verbatim all interview data prior to using framework analysis [23] for each process evaluation objective. Data and audit trail will be managed through NVivo. [name] is involved in both facilitation delivery and process evaluation. To support trustworthiness within the process evaluation, we will explicitly consider critical distance associated with the chief investigator’s ([name]) contribution to the protocol and to data interpretation. To maintain critical distance, [name] will not be involved in the fidelity sampling or assessment, as implemented successfully in an earlier study [24].

Analysis will be both inductive and deductive. The assessment of of fidelity and tailoring will largely be deductive, whilst implementation and engagement will primarily be inductive.

Data will be extracted from documents by two researchers for each of the three process evaluation objectives. The extracted data will also inform the later interview topic guides for specific sites. For example, the description of stakeholder engagement and tailoring might stimulate questions exploring the rationale for the proposed approach and/or the extent to which the plans were enacted as intended.

Analysis of fidelity of delivery will be in accordance with recommendations [21]: 80 to 100% adherence to intervention specifications represents ‘high’ fidelity of delivery, 51 to 79% represents ‘moderate’ fidelity, and < 50% or less represents ‘low’ fidelity.

Survey data will be analysed using descriptive statistics (fidelity, cost) and framework analysis (tailoring).

The analysis will be concurrent across each process evaluation objective, to enable earlier findings to inform later data collection and analysis. Interim analyses will be shared with stakeholders (including Experts by Experience, clinicians, policymakers and implementation scientists) to identify avenues for exploration within the data.

